### ***Follow-up of SAEs***

If a subject experiences an SAE, it should be followed up by the investigator (for clinical symptoms/signs, laboratory test abnormalities, or other) until it returns to normal or baseline level, or the clinical outcomes are stable. Therefore, the SAE follow-up may continue beyond the end of the study, and the sponsor may also request the SAE follow-up results after the end of the study.

### **Adverse Events of Special Interest**

"Adverse events of special interest" occurring during the study need to be reported promptly to the sponsor's medical department, safety department, or designee. The investigator should report the "adverse event of special interest" to the sponsor within 24 hours of becoming aware and record it on the Adverse Event Form of the eCRF, whether or not it is an SAE.

Adverse events of special interest include:

- ≥ Grade 3 infusion-related adverse reactions or hypersensitivity reactions;
- KN046
  - ≥ Grade 3 sensory and motor neuropathy (including Guillain-Barre syndrome, myasthenia syndrome) resulting in discontinuation of KN046;
  - Any suspected KN046 treatment-emergent serious adverse drug reactions (TESADRs) during non-hematologic treatment; uncommon TESADRs, including but not limited to, serum sickness, myocarditis, haemolytic anaemia, Lambert-Eaton syndrome, myasthenia gravis, rhabdomyolysis syndrome, partial epileptic seizure, vasculitis, and pemphigus; any treatment-related serious adverse drug reactions (TRSADRs) leading to discontinuation of KN046;
  - ≥ Grade 4 immune-related hematologic toxicity; ≥ Grade 4 skin toxicity;
  - ≥ Grade 3 immune-related pneumonia;

Version No.: 4.2

- Recurrence of Grade 2 immune-related pneumonia lasting more than 4 weeks after active treatment;
- Grade 2 immune-related central nervous system toxicity lasting more than 4 weeks after active treatment;
- $\geq$  Grade 3 immune-related colitis;
- $\geq$  Grade 3 immune-related uveitis or optic neuritis;
- $\geq$  Grade 3 immune-related hepatitis with ALT/AST  $\geq 10 \times$  ULN; or ALT/AST  $\geq 5 \times$  ULN and lasting more than 2 weeks; or ALT/AST  $\geq 5 \times$  ULN with total bilirubin  $\geq 3 \times$  ULN; or ALT/AST  $\geq 5 \times$  ULN with gastrointestinal symptoms (e.g., nausea, vomiting, tenderness of right upper abdomen);
- $\geq$  Grade 3 immune-related nephritis and renal insufficiency;
- $\geq$  Grade 1 immune-related myocarditis.
- All cardiac adverse events (whether related to KN026 or not) occurring from the dose of KN026 through 1 year after the last dose need to be reported, including the following categories. In addition, all symptomatic left ventricular systolic dysfunction occurring within 3 years after the last dose of KN026 are required to be reported.
  - Symptomatic left ventricular systolic dysfunction;
  - Asymptomatic left ventricular systolic dysfunction with the following:
    - Decrease in LVEF  $\geq 10\%$  from baseline and absolute LVEF  $< 50\%$ ;
    - Decrease in LVEF  $\geq 15\%$  from baseline.

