|                                                                                                                                                                                                                                                                                                                                        | 2                                                                                                                    | Consider dose interruption if toxicity persists | Toxicity resolves to $\leq$ Grade 1 within 12 weeks of last dose | Original dose                 | Toxicity does not resolve to $\leq$ Grade 1 within 12 weeks of last dose                                                                                                   |
|                                                                                                                                                                                                                                                                                                                                        | 3                                                                                                                    | Yes                                             | Toxicity resolves to $\leq$ Grade 1 within 12 weeks of last dose | Original dose                 | Toxicity does not resolve to $\leq$ Grade 1 within 12 weeks of last dose

Permanent discontinuation may be considered if toxicity meets the criteria for SAEs |
|                                                                                                                                                                                                                                                                                                                                        | 4                                                                                                                    | Yes                                             | N/A                                                              | N/A                           | Permanent discontinuation                                                                                                                                                  |

If KN046 treatment-related toxicity does not recover to Grade 0-1 within 12 weeks of the last dose, KN046 will be discontinued after discussion with the Sponsor's Medical Monitor.

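### The AESI list includes prolonged Grade 2 immune-related CNS toxicity but has no Grade 3 or higher CNS line, so non-serious Grade 3 CNS events fall outside it

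*Protocol*

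**What the plan says.** Protocol section 8.2.2 (Adverse Events of Special Interest) requires each AESI to reach the sponsor within 24 hours of the investigator learning of it, regardless of seriousness. Four parts of its KN046 list matter here.

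- **CNS toxicity.** One line only: "Grade 2 immune-related central nervous system toxicity lasting more than 4 weeks after active treatment".
- **Pneumonia.** Two lines: one at or above "Grade 3 immune-related pneumonia", and one for "Recurrence of Grade 2 immune-related pneumonia lasting more than 4 weeks after active treatment".
- **Neuropathy.** One line, at or above "Grade 3 sensory and motor neuropathy (including Guillain-Barre syndrome, myasthenia syndrome) resulting in discontinuation of KN046".
- **Serious reactions.** A general line: "Any suspected KN046 treatment-emergent serious adverse drug reactions (TESADRs) during non-hematologic treatment". It carries no grade threshold and no discontinuation condition. It goes on to name examples, several of them neurological: "uncommon TESADRs, including but not limited to, serum sickness, myocarditis, haemolytic anaemia, Lambert-Eaton syndrome, myasthenia gravis, rhabdomyolysis syndrome, partial epileptic seizure".

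Section 9.6.1 (Safety Endpoints) names AESI incidence as a safety result. The same sentence also lists Grade 3 or higher treatment-emergent, immune-related and treatment-related events as separate results.

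**The concern.** A list of events of special interest is normally read as rising with severity: if a given grade qualifies, a worse grade of the same toxicity does too. Pneumonia follows that logic; the CNS line does not. Read alone, it admits a moderate event that persists and leaves out a severe one.

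Two things depend on the definition: which events a site must report within 24 hours even when they are not serious, and which events enter the AESI count. The first cannot be repaired at the analysis stage, because a statistical analysis plan can regroup recorded events but cannot create an expedited report that was never required.

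The neuropathy line raises a smaller question. Whether a Grade 3 event qualifies under it depends on what is later done with KN046, not on the event itself.

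**Working it through.** No figure in the protocol bears on this, so the check sets the definitions side by side and asks which line, if any, captures each type of event.

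**Inputs**

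1. Section 8.2.2: the four parts of the AESI list described above.
2. Section 8.1.2 (Serious Adverse Event): an event is serious if it meets an outcome criterion such as death, threat to life or hospitalization, or if the investigator judges it medically significant.
3. Section 8.2 (general grade definitions, for events that CTCAE does not grade specifically): Grade 4 is life-threatening and Grade 5 is death. Grade 3 is severe and may be either serious or clinically significant; indicated hospitalization and limited self-care are among its descriptors.
4. Section 6.1.4.1, Table 2 (KN046 dose modification), non-hematologic toxicity: Grade 3 leads to interruption, with resumption possible if it resolves in time, and "Permanent discontinuation may be considered if toxicity meets the criteria for SAEs". Grade 4 leads to permanent discontinuation.

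**Capture by type of event, for events suspected to be related to KN046**

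| Event | Line that captures it | AESI? |
|---|---|---|
| CNS, Grade 2, more than 4 weeks | CNS line | Yes |
| CNS, Grade 3, serious | Serious-reaction line | Yes |
| CNS, Grade 3, not serious | None | **No** |
| CNS, Grade 4 or 5 | Serious-reaction line | Yes |
| Neuropathy, Grade 3, serious | Serious-reaction line, whether or not KN046 is stopped | Yes |
| Neuropathy, Grade 3, not serious, KN046 stopped | Neuropathy line | Yes |
| Neuropathy, Grade 3, not serious, KN046 interrupted and resumed | None | **No** |
| Neuropathy, Grade 4 or 5 | Serious-reaction line; Grade 4 also through the neuropathy line, since Table 2 requires discontinuation | Yes |

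**Are the two uncaptured rows possible?** Yes. Grade and seriousness are judged on different criteria. An event that limits self-care can be Grade 3 without hospitalization and without the investigator calling it medically significant.

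**Where the CNS wording may come from.** Section 6.1.4.1 lists toxicities for which stopping KN046 may be considered, and it contains the same Grade 2 CNS item. There the narrow wording does no harm, because Table 2 deals with Grades 3 and 4. In 8.2.2 the pneumonia, colitis, uveitis and nephritis items were widened from Grade 3 to Grade 3 or higher, and the myocarditis threshold was lowered from Grade 2 to Grade 1. The CNS item was carried over unchanged, and no table stands behind it. That suggests an oversight, but it is an inference.

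**The case against.** The strongest reply is that the list already catches the events that matter. A reader might infer from the CNS line that Grade 3 or higher CNS toxicity is never an AESI, and from the neuropathy line that severe neuropathy counts only if KN046 is stopped. Neither holds: the serious-reaction line admits Grade 4 and 5 events and serious Grade 3 events whatever is done with KN046. This stands, and it confines the point to non-serious Grade 3 events.

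A second reply is that no severe event disappears from the results, because section 9.6.1 reports Grade 3 or higher events separately from AESIs. This also stands. What is affected is the AESI count and the expedited report.

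A third reply is that 8.2.2 has no uniform threshold to depart from. Skin and hematologic toxicity start at Grade 4, myocarditis at Grade 1, and hepatitis carries extra laboratory or symptom conditions. Optic neuritis, a neurological item, has its own Grade 3 or higher entry. A discontinuation condition also appears on the list's other item for treatment-related serious reactions. This stands as far as neuropathy is concerned: the condition may be deliberate. It does not explain the CNS line. Thresholds that differ between organs are a choice; a line that takes in a lower grade and leaves out the next one up, within the same organ, is hard to read as one.

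A reader might also infer that the discontinuation condition conflicts with the 24-hour rule, because it may be met only weeks after onset. The protocol does not support that. The clock runs from awareness, and the items that require more than 4 weeks' duration mature late in the same way.

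**Conclusion.** The point holds in a limited form. On the literal text of 8.2.2, a Grade 3 immune-related CNS event that is not serious is outside the AESI count and the 24-hour AESI report, while a Grade 2 event lasting more than 4 weeks is inside both. Non-serious Grade 3 neuropathy managed by interrupting KN046 is also outside, but there the exclusion is written as an explicit condition and may be intended.

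The size cannot be put in subjects. The protocol gives no rate of immune-related neurological toxicity and no non-serious share of Grade 3 events. A figure built on an assumed overall rate would mostly count events that are already captured. The number is likely to be small, and this is a minor correction to reporting. It does not show that severe neurological toxicity goes unreported or unanalyzed.

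The conclusion rests on three assumptions:

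- The serious-reaction line is read as covering non-hematologic reactions. Its phrase about non-hematologic treatment is unclear, and a narrower reading would widen the gap.
- The events are suspected to be related to KN046.
- The Grade 3 event does not also spend more than 4 weeks at Grade 2, which would bring it in through the existing line.

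**What to change.** In section 8.2.2, keep the existing Grade 2 CNS item and add a line for Grade 3 or higher immune-related CNS toxicity beside it, as is done for pneumonia.

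Ask the sponsor to confirm whether the neuropathy item is meant to depend on KN046 being stopped. If it is, no change is needed beyond saying so. If it is not, the condition can be removed.

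Both steps concern what is reported and counted; no treatment, interruption or discontinuation rule changes. The cost is one line in the protocol and at most a few more expedited reports.

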### **Recording and Reporting of Laboratory Abnormalities and Other Abnormalities**

Laboratory test abnormalities and other abnormal study findings (e.g., ECGs) that are judged to be clinically significant, such as having related clinical symptoms and signs, leading to treatment interruption, requiring medical intervention or changing concomitant therapy, should be recorded as AEs; the laboratory test abnormalities that are judged to be not clinically significant are not required to be recorded as AEs. If a clinically significant laboratory abnormality or an abnormal vital sign is a sign of a disease or syndrome (e.g., ALP and bilirubin increased to  $> 5 \times$  ULN as a result of cholecystitis), only the diagnosis (i.e., cholecystitis) is recorded in the Adverse Event Form of the eCRF. Medical issues identified must be reported as AEs, with values above or below

the normal range indicated (e.g., "blood potassium increased" should be recorded rather than "blood potassium abnormal"); if there are corresponding standard clinical terms for the laboratory test abnormalities or vital sign abnormalities, clinical terms should be recorded in the eCRF, e.g., blood potassium increased to 5.5 mmol/L should be recorded as "hyperkalemia".

### ***Hepatic function abnormal***

The following events must be reported as AEs by the investigator to the sponsor within 24 hours of awareness with the most appropriate diagnoses or the laboratory abnormal values (when the diagnoses cannot be established) recorded on the AE Form of the eCRF, whether it is an SAE or not:

- ALT/AST  $\geq 10 \times$  ULN;
- ALT/AST  $\geq 5 \times$  ULN and lasting more than 2 weeks;
- Or ALT/AST  $\geq 5 \times$  ULN with total bilirubin  $\geq 3 \times$  ULN; or
- ALT/AST  $\geq 5 \times$  ULN with gastrointestinal symptoms (e.g., nausea, vomiting, tenderness of right upper abdomen) and treatment-emergent ALT/AST  $> 10 \times$  ULN.

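### The symptom criterion for 24-hour liver reporting in 8.2.3 is contained in the section's own first criterion, so as written it adds no case, and it does not match the parallel criterion in 8.2.2

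*Protocol*

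**What the plan says.** Two sections of the protocol set liver criteria for prompt notification.

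**Section 8.2.2, Adverse Events of Special Interest.** The deadline is: "The investigator should report the 'adverse event of special interest' to the sponsor within 24 hours of becoming aware". The liver item sits in the KN046 list and applies to events of at least "Grade 3 immune-related hepatitis with ALT/AST $\geq 10 \times$ ULN; or ALT/AST $\geq 5 \times$ ULN and lasting more than 2 weeks". Two further alternatives follow: ALT/AST of at least 5 x ULN with total bilirubin of at least 3 x ULN, and ALT/AST of at least 5 x "ULN with gastrointestinal symptoms (e.g., nausea, vomiting, tenderness of right upper abdomen"). The symptom alternative stops there.

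**Section 8.2.3, Hepatic function abnormal.** The introduction reads: "The following events must be reported as AEs by the investigator to the sponsor within 24 hours of awareness". It carries no immune-related condition and applies whether or not the event is an SAE. Its first bullet is "ALT/AST $\geq 10 \times$ ULN" with nothing further required. The second and third bullets are the same duration and bilirubin alternatives as in 8.2.2. The fourth starts from ALT/AST of at least 5 x ULN with gastrointestinal symptoms and then adds a second laboratory condition: "e.g., nausea, vomiting, tenderness of right upper abdomen) and treatment-emergent ALT/AST $> 10 \times$ ULN".

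**The concern.** A list of alternatives should give each item some work to do. Here the fourth bullet names a threshold of 5 x ULN and then, as written, requires a value above 10 x ULN, which is already enough under the first bullet. The symptom criterion in 8.2.2 has no such addition, so two lists that otherwise share the same laboratory conditions and the same deadline disagree on this one.

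Prompt notification of symptomatic liver injury is at stake. For a liver event not judged immune-related, 8.2.3 is the only liver-specific 24-hour rule: the special-interest item in 8.2.2 requires immune-related hepatitis, and the items there tied to KN026 are cardiac. Both drugs are given together, and the protocol's background section reports transaminase rises with each, so the immune-related judgement will not always be easy. Where the answer is no, the sponsor loses early notice of the symptomatic events that the fourth bullet appears meant to catch.

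**Working it through.** The plan states no figure on this point, so there is none to reproduce. The check is a comparison of logical rules.

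**Notation.** Let x be ALT/AST in multiples of ULN, D a rise lasting more than 2 weeks, B total bilirubin of at least 3 x ULN, and S gastrointestinal symptoms.

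**Rules as written.**
- 8.2.2, given immune-related hepatitis of Grade 3 or higher: x ≥ 10, or (x ≥ 5 and D), or (x ≥ 5 and B), or (x ≥ 5 and S).
- 8.2.3, any cause, literal reading: x ≥ 10, or (x ≥ 5 and D), or (x ≥ 5 and B), or (x ≥ 5 and S and x > 10).

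**Step 1: what the fourth bullet of 8.2.3 adds.** The condition x ≥ 5 and S and x > 10 reduces to S and x > 10. Every x > 10 satisfies x ≥ 10, which is the first bullet. The fourth bullet is a subset of the first and adds no case.

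**Step 2: where the two lists differ.** Both rules were evaluated at x = 4.9, 5, 7.5, 9.9, 10, 10.1 and 15 with D, B and S each present or absent, which gives 7 x 2 x 2 x 2 = 56 combinations. For an event that qualifies for 8.2.2, the two lists disagree in three: x = 5, 7.5 and 9.9 with S present and D and B absent. With symptoms present and neither duration nor bilirubin met:

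| ALT/AST (x ULN) | 8.2.2, immune-related | 8.2.3, literal | 8.2.3, clause removed or read as a separate item |
|---|---|---|---|
| 4.9 | no | no | no |
| 5 | yes | no | yes |
| 7.5 | yes | no | yes |
| 9.9 | yes | no | yes |
| 10 | yes | yes | yes |
| 10.1 | yes | yes | yes |
| 15 | yes | yes | yes |

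**Step 3: the alternative reading.** If *and* introduces a separate item (x > 10 alone), that item lies inside the first bullet and is redundant. The symptom criterion then works from 5 x ULN, and the ALT/AST conditions match those of 8.2.2 in all 56 combinations.

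**Step 4: who escapes a 24-hour report altogether.** Both lists apply together, and SAEs have their own 24-hour rule in 8.2.1. Under the literal reading, an event is missed only if all of these hold:
- x is at least 5 and below 10, with gastrointestinal symptoms;
- it lasts 2 weeks or less;
- total bilirubin is below 3 x ULN;
- it is not judged immune-related, so 8.2.2 does not apply;
- it is not an SAE.

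**The case against.** The strongest reply is that this is a drafting slip with little consequence. Most of that stands.

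- **The events are not lost.** Section 8.2.3 itself requires clinically significant laboratory abnormalities, including those with related symptoms, to be recorded as AEs. Section 9.6.1 then analyses treatment-emergent events, those of Grade 3 or higher, and Grade 3 or 4 laboratory abnormalities. A reader might infer that the combination's liver signal is under-counted. The protocol does not support that: notification is slower, but the event stays in the safety data.
- **Special-interest counts do not move.** A reader might also infer that this safety output is distorted. Events of special interest are defined in 8.2.2, where the symptom criterion already works from 5 x ULN. The hepatic bullets of 8.2.3 define none.
- **Failing one list does not cancel the other.** An immune-related symptomatic rise that qualifies under 8.2.2 is still due within 24 hours, as is any SAE. Restricting the 8.2.2 item to immune-related hepatitis may well be intended, since KN046 is a checkpoint inhibitor.
- **The list looks garbled.** The third bullet both opens and closes with *or*, so the trailing clause may be a separate item that was run on. It would then be redundant and harmless. The text does not say so, however, and a site reading it as written will apply the joint condition.

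What remains after these replies is narrow but certain: on the literal reading the symptom criterion has no effect, on the other reading the clause has none, and the bullet needs correction either way.

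**Conclusion.** The point holds as an internal inconsistency in an expedited safety-reporting rule. The containment of the fourth bullet in the first is a matter of logic and rests on no assumption about rates. That symptomatic events go without a 24-hour report does depend on the literal reading of *and*.

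The affected group is the one defined in step 4 of the working. Its size cannot be estimated from the protocol and is likely small. It may be tempting to build a count from the ALT-increase rates in the background section (7.9%, 14.3%, 16%, 19.3% and 24.1% across studies). Those rates carry no 5 x ULN threshold, the 14.3% and 24.1% come from studies combining a study drug with chemotherapy, and nothing in the protocol gives the fraction passing the further filters on symptoms, duration, bilirubin, attribution and seriousness. No number of subjects, and no share of all reportable liver events, should be quoted.

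ORR, DOR, the sample size and the analysis sets are not affected.

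**What to change.** Reconcile the fourth hepatic bullet of 8.2.3 with the symptom criterion of 8.2.2. One way is to delete the appended condition on treatment-emergent ALT/AST above 10 x ULN, which makes the ALT/AST conditions of the two lists identical. If the clause was meant as a separate item, it can equally be dropped, because the first bullet already covers it. The difference in scope, immune-related hepatitis in 8.2.2 and any cause in 8.2.3, would remain; one sentence confirming that it is intended would help sites.

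The cost is one clause in the next amendment, matching text in the eCRF and safety-reporting guidance, and a few more 24-hour reports. The change concerns reporting only; no dose or treatment rule is proposed.
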